## **6. Data Management**

### **6.1. Data Sources**

The investigators have previously designed and implemented the Calgary Registry for Advanced and Therapeutic Endoscopy (CReATE, University of Calgary Conjoint Health Research Ethics Board 18-0410). CReATE is a high-fidelity prospective database that seeks to answer questions in ERCP outcomes research. As such, over 400 data fields are collected in real-time for each ERCP procedure, including detailed patient-, endoscopist- and procedure-based

variables. Therefore, CReATE serves as the ideal data collection platform for this randomized trial.

Data are inputted by a full-time research assistant, and stored and managed on a secure web application specializing in healthcare database implementation and maintenance, REDCap. This web portal allows for facile access to secure data. The web portal is secured by the latest security technology. Study participants will be identifiable on the secure platform for purposes of patient contact, follow-up and potential withdrawal. For the purposes of this randomized study, an additional tab will be created in the electronic interface that will allow for entry of the arm to which the patient has been randomized. Whenever data are exported for analysis, they will be de-identified and assigned unique study codes only. The primary investigator will be the custodian of the identifiable electronic data, which will be stored only on a secure server accessible only via combination of password protection and temporary electronic fob.

## **6.2. Study Variables**

As part of CReATE, several patient-, endoscopist- and procedure-related variables are routinely collected. These will all be available to analyze as part of this proposed study. Variables include:

- patient-related:
  - age
  - sex
  - comorbidities
  - surgical history
  - social history
- endoscopist-related:
  - experience and procedural volume of endoscopist
  - presence and stage of trainees
  - degree of procedural involvement of trainees
- procedure-related:
  - indication for ERCP
  - history of prior ERCP(s)
  - luminal and biliary anatomy

- details of procedure (appearance of papilla, intended duct(s) of interest, cannulation attempts and time, findings/appearance of duct(s), pathology)
- instruments and devices used
- stent(s) placed
- procedural success
- cannulation time
- procedure time
- intraprocedural adverse event(s)
- sedating medications used
- post-procedural:
  - patient pain and satisfaction scores
  - early and late adverse events within 30 days
  - unplanned presentation to acute care facility or readmission within 30 days, with details.

## 7. Study Outcomes

### 7.1. Primary Outcomes

There are two co-primary outcomes for this study. The first primary outcome of the study is the **ERCP technical success rate** with the ED34-i10T2 duodenoscope and DEC, compared to the currently available duodenoscope (ED34-i10T). Technical success will be determined in duplicate by two blinded outcome adjudicators with no knowledge of the patient's allocation in the study. The adjudicators will review redacted and de-identified procedure reports for each study patient, and determine the presence or absence of technical success of the overall procedure based on a set of *a priori* definitions (see below). Any potential disagreements will be resolved by a third blinded adjudicator. Technical success will also be determined subjectively on a case-by-case basis by the endoscopist performing the procedure, in order to measure correlation with the adjudicator determinations, but not to be used in the determination of the co-primary outcome. Failure of the procedure due to inability to safely perform the procedure under conscious sedation will not constitute a technical failure for purposes of this study, in either study arm. The second co-primary outcome is the **persistent bacterial contamination rate** with the ED34-i10T2

duodenoscope and DEC, compared to the currently available duodenoscope (ED34-i10T) following standardized disinfection and reprocessing. This will be defined as:

- any growth of  $\geq 10$  colony-forming units (CFUs) at 72 hours, and/or
- any growth of one or more Gram-negative pathogen regardless of CFU count.

### **7.1.1 Definitions of Technical Success**

Technical success will be dependent on the indication for the ERCP, as shown in Table 1. These definitions will be used by the blinded adjudicators to determine the presence or absence of technical success on a case-by-case basis.

Table 1. Definitions of Technical Success by ERCP Indication.

| Indication for ERCP                                                                                                                                                                                                                                                                                                                              | Definition(s) of Technical Success                                                                                                                                                                                                                                         |
|---------------------------------------------------------------------------------------------------------------------------------------------------------------------------------------------------------------------------------------------------------------------------------------------------------------------------------------------------------|-----------------------------------------------------------------------------------------------------------------------------------------------------------------------------------------------------------------------------------------------------------------------------------|
| Suspected or confirmed bile duct stone(s)                                                                                                                                                                                                                                                                                                               | Extraction of stone(s)

OR

CBD clearance based on absence of filling defects on occlusion cholangiogram

*If difficult biliary stones are encountered during procedure, use 'Difficult biliary stone(s)' indication below, and above definition does not apply |
| Difficult biliary stone(s)  – any of: 
 
• One or more stone(s) <math>\geq 15</math> mm
 
• Barrel or other unusual shape
 
• Multiple (4 or more stones)
 
• Impacted stone(s)
 
• Intrahepatic or cystic duct stone(s)
 
• Stricture below stone(s)
 
 | Extraction of stone(s)

OR

CBD clearance based on absence of filling defects on occlusion cholangiogram

OR

Stenting of CBD as part of future plan to clear duct                                                                                        |
| Biliary stricture (benign or malignant)                                                                                                                                                                                                                                                                                                                 | Successful placement of stent with proximal margin proximal to stricture

OR

Successful dilatation of stricture                                                                                                                                                      |
| Cholangioscopy or pancreatoscopy                                                                                                                                                                                                                                                                                                                        | Successful cholangioscopic or pancreatoscopic visualization of area of interest                                                                                                                                                                                                   |
| Chronic pancreatitis, pancreatic stone(s) and/or pancreatic stricture(s)                                                                                                                                                                                                                                                                                | Successful cannulation of main pancreatic duct (PD)

AND AT LEAST 1 OF:

Pancreatic sphincterotomy
Stenting or dilatation of PD
Extraction of PD stone(s)                                                                                                       |
| Pancreas divisum                                                                                                                                                                                                                                                                                                                                        | Successful minor papilla cannulation                                                                                                                                                                                                                                              |

|                                      |                                                |
|--------------------------------------|------------------------------------------------|
|                                      | AND                                            |
|                                      | Successful pancreatic sphincterotomy           |
| Stent removal or exchange            | Successful removal and/or exchange of stent(s) |
| Treatment of peri-ampullary bleeding | Successful endoscopic hemostasis               |
| Sphincter of Oddi dysfunction        | Successful biliary sphincterotomy              |

Furthermore, the reason(s) for technical failure will be documented by the adjudicators as per the procedural report (Table 2).

Table 2. Reasons for Technical Failure by ERCP Indication.

| Reason(s) for Technical Failure                                                                                                                                                                                          |
|---------------------------------------------------------------------------------------------------------------------------------------------------------------------------------------------------------------------------------|
| Inability to locate papilla in patient with normal anatomy                                                                                                                                                                      |
| Inability to locate papilla in patient with altered anatomy, including: 
 
• duodenal or peri-ampullary diverticulum
 
• Billroth II surgery
 
• Roux-en-Y surgery
 
 |
| Inability to achieve an en-face view of the papilla of interest due to a luminal stricture                                                                                                                                      |
| Inability to cannulate duct of interest                                                                                                                                                                                         |
| Inability to perform sphincterotomy when necessary                                                                                                                                                                              |
| Inability to clear duct of interest                                                                                                                                                                                             |
| Inability to place stent proximal to area of interest                                                                                                                                                                           |
| Inability to remove or exchange stent                                                                                                                                                                                           |
| Inability to achieve hemostasis endoscopically                                                                                                                                                                                  |
| Inability to successfully load, exchange or remove devices necessary for the completion of the procedure                                                                                                                        |
| Inability to safely complete procedure due to issues with sedation*                                                                                                                                                             |
| *If this is the only reason for technical failure, the patient will be excluded from final analysis                                                                                                                             |

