## **9. Statistical Considerations**

### **9.1. Hypothesis and Sample Size Calculations**

The first co-primary outcome considers technical success of the ERCP procedure. Overall technical success rates in ERCP vary widely depending on the definitions employed. It is widely agreed upon that a cannulation rate greater than 90% (in native papillae) is an attainable key performance indicator (KPI) in ERCP performed for choledocholithiasis. However, in cases of malignant biliary obstruction, especially at low-volume centers, cannulation rates appear to be significantly lower. When one considers overall procedural success rate, these targets become even less clear, with studies reporting between 60 and 90% success rates depending on the definitions employed.

Prospective data from our center have been analyzed to assess our group's rates, based on 10 months of procedures in over 600 patients having undergone ERCP. Deep cannulation rates in native papillae at our center are approximately 96%. Overall procedural success in all-comers is approximately 92%, with 4% representing cannulation failures, 4% representing inability to clear or relieve obstruction in the duct(s) of interest.

Thus, when comparing clinical efficacy between DEC and traditional duodenoscopes, we selected an overall baseline technical success rate of 92% based on our experience. We propose that technical success of DEC within a margin of 7% of traditional duodenoscopes will result in an ability to conclude non-inferiority of DEC. A hypothesis will therefore be tested that the overall technical success rate with DEC will be at least 85%:

$$H_0: P_{CON} \geq P_{DEC} + d \text{ (Inferior)} \quad H_1: P_{CON} - d < P_{DEC} \text{ (Non-inferior)}$$

where  $P_{DEC}$  is the overall technical success rate for DEC in this study,  $P_{CON}$  is the overall technical success rate for traditionally designed duodenoscopes (control),  $d$  is the set non-inferiority limit of 7%, and  $H_0$  and  $H_1$  are the null and alternate hypotheses, respectively.

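### The difficult-stone row of Table 1 admits intrahepatic and cystic duct stones, but one of its success criteria checks only the common bile duct

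*Supplement*

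**What the plan says.** This concerns the latest protocol, section 7.1.1, and the SAP.

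- **Entry to the row.** Any one of six features puts a patient in the difficult-stone row of Table 1. One of them is location: "Intrahepatic or cystic duct stone(s". The ordinary bile duct stone row passes such cases on: "If difficult biliary stones are encountered during procedure, use 'Difficult biliary stone(s)' indication below, and above definition does not apply".
- **Success in the row.** Three criteria are joined by OR: "Extraction of stone(s"; "CBD clearance based on absence of filling defects on occlusion cholangiogram"; "Stenting of CBD as part of future plan to clear duct". None is tied to where the stone lies.
- **Status of Table 1.** "These definitions will be used by the blinded adjudicators to determine the presence or absence of technical success on a case-by-case basis". Under section 7.1 the endoscopist's own view of success is recorded but does not enter the co-primary outcome.
- **Table 2.** This lists reasons for technical failure, among them "Inability to clear duct of interest".
- **Planning baseline.** Section 9.1 states "we selected an overall baseline technical success rate of 92% based on our experience". It splits the 8% of failures into 4% cannulation failures and 4% failures to clear, or relieve obstruction in, the duct or ducts of interest.
- **SAP.** The data dictionary (section B) codes technical success as 0 or 1 and adds no definition.

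**The concern.** The row covers stones in three places (CBD, intrahepatic ducts, cystic duct), but its second criterion inspects only one of them. If the only stone is intrahepatic or in the cystic duct, the CBD may show no filling defect from the outset. The criterion is then met although the target was never reached.

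Technical success is the non-inferiority co-primary outcome. Scoring untreated targets as successes in both arms removes failures from both. If DEC leaves more of these stones untreated than control, more failures are removed from the DEC arm, and the observed difference shrinks towards zero. In a non-inferiority comparison that favours the new device.

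**Working it through.** **1. Reading the rule.** Take a patient with one intrahepatic stone, a cannulated bile duct, no CBD filling defect on occlusion cholangiogram, no extraction and no stent.

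| Table 1 criterion | Met? |
|---|---|
| Stone extraction | No |
| CBD clearance on occlusion cholangiogram | Yes |
| CBD stent with a plan to clear later | No |
| Result (OR) | Technical success |

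No other current text requires clearance of the intrahepatic or cystic duct. The baseline in section 9.1 and the wording of Table 2 both speak of the duct of interest, which suggests that the target duct was meant.

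**2. The plan's own sample size.** Inputs from section 9.1: 92% in both arms, margin 7 points, one-sided alpha 0.025, power 80%.

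n per arm = (1.960 + 0.842)² × 2 × 0.92 × 0.08 / 0.07² = 235.8, rounded up to 236. This matches the protocol. The SAP (section A) lists 518 patients for this outcome, which is 259 per arm.

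**3. Size of the effect.** The documents give neither the share *c* of patients whose only stone lies outside the CBD nor the rates *f* at which such stones go untreated by arm. Both are assumed here. Taking every untreated stone as rescued by the CBD criterion:

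- measured rate = true rate + c × f
- difference erased = c × (f for DEC − f for control)
- false non-inferiority rate = Φ(erased / SE − 1.96), with the true difference at the margin (92% v 85%)
- SE = √[(p₁(1 − p₁) + p₂(1 − p₂)) / 259], using the measured rates p₁ and p₂

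This is a normal approximation, not the exact test that the protocol names.

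Worked case: c = 2%, f = 30% control and 50% DEC. The measured rates are 92.6% and 86.0%, so 7.0 − 6.6 = 0.4 points are erased. SE = 0.0270, and Φ(0.004/0.0270 − 1.96) = Φ(−1.81) = 3.5%.

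| Untreated, control v DEC | c = 1% | c = 2% | c = 3% |
|---|---|---|---|
| 30% v 50%: points erased | 0.2 | 0.4 | 0.6 |
| 30% v 50%: false non-inferiority | 3.0% | 3.5% | 4.1% |
| 8% v 15%: points erased | 0.07 | 0.14 | 0.21 |
| 8% v 15%: false non-inferiority | 2.65% | 2.8% | 3.0% |
| 40% v 40%: points erased | 0 | 0 | 0 |
| 40% v 40%: false non-inferiority | 2.5% | 2.5% | 2.5% |

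The 8% v 15% rows apply the overall failure rates (100 − 92 and 100 − 85) to this subgroup.

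**4. Allowing for the stenting criterion.** If half of the untreated stones would have counted as successes through stenting anyway (an assumption), the 30% v 50% case falls to 0.1, 0.2 and 0.3 points, and the error rates to about 2.7%, 3.0% and 3.2%.

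**The case against.** The best case for leaving the row alone has four parts.

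- **Success is not automatic.** A reader might infer that these patients succeed whichever scope is used. The documents do not support that. An occlusion cholangiogram requires the papilla to be reached and the duct cannulated, and cannulation failure makes up 4 of the 8 points of baseline failure. Only a deficit that arises after cannulation can be hidden. This part stands.
- **Table 2 does not contradict Table 1.** A reader might infer that the same patient is a success in one table and a failure in the other. But Table 2 only records why a procedure already judged a failure has failed, so a Table 1 success receives no Table 2 reason. Its wording is evidence of intent, no more. This part stands too.
- **The stenting criterion already accepts a stone left in place.** It appears to be a deliberate choice for this row, and it would make some of these patients successes whatever the clearance wording says. That reduces the size of the effect but does not remove the gap for patients who are not stented.
- **Adjudicators may read the row as intended.** They are blinded and work in duplicate, with a third to settle disagreements. That settles a dispute but does not supply the missing rule, and section 7.1.1 tells them to apply Table 1.

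**Conclusion.** The point holds as a gap in one criterion of one row. Read as written, Table 1 scores an untreated stone outside the CBD as a technical success once the CBD is shown to be clear.

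The consequence is conditional. A reader might infer a bias that always favours DEC. That follows only if DEC leaves more of these stones untreated, and nothing in the documents shows that it does. With equal rates there is no bias in the difference.

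Under the assumptions above, between 0 and 0.6 points of the 7-point margin are erased and the false non-inferiority rate is 2.5% to 4.1%. The upper end needs both a 3% share and a 20-point gap between arms in untreated stones. With the overall failure rates of 8% v 15% it is about 2.65% to 3.0%. All of these figures are lower where stenting would have applied anyway. This is a minor point, worth correcting because the correction is cheap.

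**What to change.** In the difficult-stone row of Table 1, replace CBD clearance with clearance of the duct(s) of interest, defined as the duct or ducts holding the target stone(s), on occlusion cholangiogram. Leave the extraction and stenting criteria as they are. The row then agrees with the wording of Table 2 and with the basis of the 92% baseline.

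The SAP already gives patient counts, so adjudication may be complete. In that case, keep the adjudicated result as the primary analysis, have blinded adjudicators rescore these patients from the existing procedure reports under the amended wording, and report the result as a sensitivity analysis. Also report how many patients in each arm had stones only outside the CBD, since that number bounds the effect.

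The cost is one phrase and possibly a slightly lower observed success rate. No new data field, visit or change in sample size is needed.

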## **7.2. Secondary Outcomes**

The following will be recorded as secondary outcomes for the study:

- clinical success rate, defined as technical success rate in addition to a lack of repeat unplanned endoscopy, imaging, emergency department presentation, admission within 30 days of the index procedure for reasons related to ongoing pancreaticobiliary pathology that was initially thought to be resolved after the initial ERCP;
- subjective presence or absence of technical success as deemed by the endoscopist;
- assessment of overall ease of use of duodenoscope, using Likert scale of 1-10;
- procedure time;
- device failure or dislodgement rate of the disposable cap;
- overall adverse event rate (intraprocedural, early and late) and severity as defined and graded by the American Society for Gastrointestinal Endoscopy (ASGE) Lexicon within 30 days of the index procedure;
- pancreatitis rate, as defined by new or distinct abdominal pain after ERCP in addition to lipase rise above 3 times the upper limit of normal within 30 days of the index procedure;
- bleeding rate, as defined by hematemesis and/or melena and/or hematochezia, or drop in hemoglobin by  $\geq 2 \text{ g}^{23}$  following ERCP with either sphincterotomy or sphincteroplasty (or both) within 30 days of the index procedure;
- cholangitis and/or sepsis rate within 30 days of the index procedure;
- hospital admission or unplanned presentation to an acute healthcare facility within 30 days of the index procedure;
- mortality rate within 30 days of the index procedure;
- manual post-ERCP disinfection time (in endoscopy unit);
- reprocessing time (in automated reprocessing room).

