### **8.5. Follow-up**

Patients will be contacted by the RA by telephone 30 days following their ERCP to assess for any ongoing symptoms and advise of any adverse events, including unplanned emergency department visits or inpatient admissions. The patient's medical record is also reviewed at 30 days for complete details of any unplanned emergency department visits, inpatient admissions or prolonged admissions.

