## **8.6. End-of-Study Definition**

This clinical trial will be considered complete when participants are no longer being examined or the last participant's final 30-day follow-up check has occurred. A participant will be considered to have completed the study if he or she has completed the index procedure in addition to the follow-up phone assessment at the 30-day timepoint.

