**A) Data groups:**

1. MICROBIOLOGY OUTCOME – co-primary outcome 1 (superiority outcome). N = 422 patients.
2. TECHNICAL OUTCOME – co-primary outcome 2 (non-inferiority outcome). N = 518 patients.
3. SAFETY OUTCOMES AND SECONDARY OUTCOMES. N = 518 patients.

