**B) Variables and data dictionary:**

| Variable Name | Description/ Definition                                            | Coding                             |
|-----------------------------|----------------------------------------------------------------------------------|--------------------------------------------------|
| study_id                    | unique study identifier                                                          | (whole number)                                   |
| scope_random                | study randomization and allocation                                               | 1 = scope design A; 2 = scope design B (blinded) |
| tech_outcome                | technical success, co-primary outcome #1 (non-inferiority)                       | 0 = unsuccessful; 1 = successful                 |
| micro_outcome               | persistent microbial contamination, co-primary outcome #2 (superiority)          | 0 = no event; 1 = event                          |
| ae_pancreatitis             | pancreatitis following ERCP (ascertained at 30-day follow-up)                    | 0 = no event; 1 = event                          |
| ae_bleeding                 | bleeding following ERCP (ascertained at 30-day follow-up)                        | 0 = no event; 1 = event                          |
| ae_perforation              | perforation following ERCP (ascertained at 30-day follow-up)                     | 0 = no event; 1 = event                          |
| ae_cholang                  | cholangitis following ERCP (ascertained at 30-day follow-up)                     | 0 = no event; 1 = event                          |
| ae_cardio_resp              | cardiorespiratory adverse event following ERCP (ascertained at 30-day follow-up) | 0 = no event; 1 = event                          |
| ae_death                    | death following ERCP (ascertained at 30-day follow-up)                           | 0 = no event; 1 = event                          |
| ice_duo_num                 | duodenoscope number                                                              | (one of several pre-specified numbers)           |
| ice_duo_ease_md             | ease of use of overall scope design, according to endoscopist/trainee            | (scale from 0 to 10)                             |

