### C) ANALYSIS

Two-tailed Fisher's exact tests and chi-squared tests will be used to compare proportions. Outcomes will be compared between groups in an intention-to-treat analysis without adjustment. Comparisons will be reported using relative risks (RRs) and numbers needed to treat (NNTs) along with their respective 95% confidence intervals (CIs).

*Post hoc* subgroup analyses will be performed on sex (female or male), age (<65 or ≥65 years), study site (Calgary or Kingston), procedural complexity (1-2 or 3-4), papilla status (native

papilla or prior sphincterotomy), disposition (inpatient or outpatient), biliary stent placement (present or none), and indication (suspected or confirmed malignancy or all others). All statistical analyses will be performed using RStudio version 1.2.1335 (Integrated Development Environment for R, Boston, USA).

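### Clinical success does not require survival to day 30, so a technically successful patient who dies before a qualifying return event is scored a success

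*Supplement*

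**What the plan says.** Protocol section 7.2 (latest version) lists the outcome as "clinical success rate, defined as technical success rate in addition to a lack of repeat unplanned endoscopy, imaging, emergency department presentation, admission within 30 days". The sentence continues with a restriction by cause: the return event counts only "for reasons related to ongoing pancreaticobiliary pathology that was initially thought to be resolved after the initial ERCP".

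Death is a separate item in the same list: "mortality rate within 30 days of the index procedure". The SAP data dictionary (part B) holds it as a stand-alone 0/1 variable, ae_death, described as "death following ERCP (ascertained at 30-day follow-up". The dictionary has no variable for clinical success.

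SAP part A sets the data group for this outcome: "SAFETY OUTCOMES AND SECONDARY OUTCOMES. N = 518 patients". SAP part C sets the comparison: "Outcomes will be compared between groups in an intention-to-treat analysis without adjustment". Neither part says how a death before day 30 enters an outcome measured over 30 days.

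On ascertainment, the Follow-up section of the protocol adds a record check to the 30-day telephone call: "The patient's medical record is also reviewed at 30 days for complete details of any unplanned emergency department visits, inpatient admissions or prolonged admissions". Section 8.6 says who has completed the study ("A participant will be considered to have completed the study if he or she has completed the index procedure", together with the 30-day call), but does not make completion a condition for being analysed.

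**The concern.** Once technical success is achieved, a patient can fail this outcome only through an unplanned repeat endoscopy, imaging, an emergency visit or an admission. Someone who dies first has none of these and so meets the definition. The clearest case is an inpatient who has a technically successful ERCP, deteriorates from biliary sepsis and dies in the same stay. There is no emergency presentation and no new admission to count. Unless unplanned imaging or endoscopy was done and attributed to ongoing pancreaticobiliary disease, the patient is recorded as a clinical success.

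The path is plausible in this trial. Section 5.2 admits patients needing ERCP for any indication, and the SAP codes malignant obstruction and cholangitis among the indications and inpatients as a disposition. At stake is the meaning of the clinical success rate and of the relative risk and NNT computed from it. Some patients with the worst possible outcome would sit in the success count, and a reader of the report could not tell how many.

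**Working it through.** The documents state no figure for clinical success, so there is no planned number to reproduce. The check has two parts.

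**1. Does the text score the path, and does anything override it?**

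- *Definition (protocol 7.2):* two conditions, technical success and absence of four kinds of event. Being alive at day 30 is not a third.
- *Mortality (protocol 7.2; SAP part B):* collected, but not linked to clinical success.
- *Analysis set (SAP parts A and C):* 518 patients, intention-to-treat, unadjusted. No rule removes or recodes deaths.
- *Completion (protocol 8.6):* defines completers, but does not drop non-completers from analysis.
- *Follow-up:* record review covers visits, admissions and prolonged admissions. A prolonged index admission is not a failure component in 7.2.

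The definition therefore applies as written. It affects only deaths that follow technical success and precede a qualifying return event. Deaths after technical failure or after a qualifying event are already failures.

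**2. How large is the effect?**

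Inputs:
- Patients per arm: 518 / 2 = 259 (SAP part A, assuming an equal split under 1:1 allocation).
- Technical success: 92% (protocol 9.1).
- *d*, risk of death before any return event: not in the documents; assumed 1 to 4%, which is 2.6 to 10.4 deaths per arm of 259.
- *r*, risk of a qualifying return event among technical successes who survive: not in the documents; assumed 5 to 20%.
- Death is taken as independent of technical success, for illustration.

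One affected death, compared with scoring it as failure: 1 / 259 = 0.39 points.

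Arm-level rates:
- As written: 0.92 × [(1 − d)(1 − r) + d]
- Death scored as failure: 0.92 × (1 − d)(1 − r)
- No deaths, or deaths excluded: 0.92 × (1 − r)

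Subtracting, the written rule exceeds death-as-failure by 0.92 × d, and exceeds no deaths (or exclusion) by 0.92 × d × r.

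| d | r | As written | Death = failure | No deaths / excluded | Rise v failure | Rise v no deaths |
|---|---|---|---|---|---|---|
| 1% | 5% | 87.45% | 86.53% | 87.40% | 0.92 pts | 0.05 pts |
| 2% | 10% | 82.98% | 81.14% | 82.80% | 1.84 pts | 0.18 pts |
| 4% | 20% | 74.34% | 70.66% | 73.60% | 3.68 pts | 0.74 pts |

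For scale, if an arm's rate were about 85% (an assumption), its standard error would be √(0.85 × 0.15 / 259) = 2.2 points, and that of a difference between arms √2 × 2.2 = 3.1 points.

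**The case against.** The strongest case against is that this outcome is not meant to measure survival. It is restricted by cause and asks whether the treated problem stayed resolved. On that reading, a cancer or cardiac death after lasting drainage is not plainly a clinical failure, and calling every death a failure would put an unrestricted component into a cause-restricted outcome. This stands in part. How to score unrelated deaths is a choice of estimand, and the fix should carry both versions. It does not rescue the written rule, which also scores as success a death from the very disease, or the procedure, that the outcome is about.

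A reader might also infer that an arm's success rate is lifted by several points through its deaths, so that the arm with more deaths gains materially. The documents do not support that size. The 0.92 to 3.68 points above measure the effect of switching to death-as-failure. The gain over no deaths is confined to patients who would otherwise have had a return event, hence 0.05 to 0.74 points. Between arms, an invented imbalance of 8 v 2 deaths would give 6/259 × 0.92 = 2.1 points against death-as-failure, but only 0.1 to 0.4 points (2.1 × r) against no deaths. The documents give no reason to expect such an imbalance between two duodenoscope designs, and without one there is little distortion of the comparison.

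Nor are deaths hidden: mortality is its own outcome in the same list, so an imbalance would be visible. Repeat endoscopy and imaging can also occur during the index stay and catch some deteriorating patients. Both points reduce the consequence. Neither corrects the clinical success rate or shows which deaths were counted in it.

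**Conclusion.** The point holds in a limited form. As written, clinical success includes technically successful patients who die within 30 days before a qualifying return event, whatever the cause of death, and neither the latest protocol nor the SAP overrides this. Each such death is worth 0.39 points of an arm's rate compared with scoring it as failure. Compared with no deaths or with excluding them, the rise is about 0.05 to 0.74 points. That range rests on assumed mortality of 1 to 4%, assumed return-event risk of 5 to 20%, the protocol's 92% technical success, and independence of death and technical success.

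This is one of 13 secondary outcomes. Neither co-primary outcome, the sample size nor the non-inferiority conclusion depends on it. It is worth correcting because the rule gives a wrong score to deaths from pancreaticobiliary or procedural causes and because the correction is cheap, not because a large bias has been shown.

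**What to change.** In protocol 7.2 and the SAP, state that a patient who dies from any cause within 30 days of the index procedure is not a clinical success, derived from ae_death. Add a clinical-success variable to the SAP data dictionary with its full derivation: technical success, the qualifying return events with their restriction by cause, and death. Alongside it, report a version in which only pancreaticobiliary or ERCP-related deaths count as failures, in keeping with that restriction. Settle the rule while the allocation code in the SAP is still blinded.

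The cost is a sentence in each document and one derived variable. The death indicator is already collected, but the cause-related version also needs a cause of death for each case, which the SAP dictionary does not list. Success rates will be slightly lower, and in the all-cause version some deaths unrelated to the treated problem will count as failures. The second version shows how much that matters.
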